## Abstract

**Background:**

Smoking-related cues can trigger drug-seeking behaviors, and computer-based interventions that reduce cognitive biases towards such cues may be efficacious and cost-effective cessation aids. In order to optimize such interventions, there needs to be better understanding of the mechanisms underlying the effects of cognitive bias modification (CBM). Here we present a protocol for an investigation of the neural effects of CBM and varenicline in non-quitting daily smokers.

**Methods/Design:**

We will recruit 72 daily smokers who report smoking at least 10 manufactured cigarettes or 15 roll-ups per day and who smoke within one hour of waking. Participants will attend two sessions approximately one week apart. At the first session participants will be screened for eligibility and randomized to receive either varenicline or a placebo over a seven-day period. On the final drug-taking day (day seven) participants will attend a second session and be further randomized to one of three CBM conditions (training towards smoking cues, training away from smoking cues, or control training). Participants will then undergo a functional magnetic resonance imaging scan during which they will view smoking-related pictorial cues. Primary outcome measures are changes in cognitive bias as measured by the visual dot-probe task, and neural responses to smoking-related cues. Secondary outcome measures will be cognitive bias as measured by a transfer task (modified Stroop test of smoking-related cognitive bias) and subjective mood and cigarette craving.

**Discussion:**

This study will add to the relatively small literature examining the effects of CBM in addictions. It will address novel questions regarding the neural effects of CBM. It will also investigate whether varenicline treatment alters neural response to smoking-related cues. These findings will inform future research that can develop behavioral treatments that target relapse prevention.

**Trial registration:**

Registered with Current Controlled Trials: ISRCTN65690030. Registered on 30 January 2014.

## Background

Smoking remains a significant public health concern, with tobacco-related deaths being estimated at around 6 million per year [1]. Despite many smokers reporting wanting to quit, few achieve long-term abstinence. Many episodes of drug relapse, including relapse to smoking, occur in the presence of drug-related cues [2, 3]. Through repeated and contingent pairing with drug administration, these cues acquire powerful motivational properties that can precipitate craving and drug-seeking [4–7]. Drug-related cognitive biases, characterized by selective or disproportionate attention allocation to drug cues, have been reported in users of a number of drugs and have been positively associated with drug craving [8, 9], future drug use [10], approach behaviors to drug-related cues [11], and increased likelihood of relapse [12]. Of particular importance, the drug-stimulus learning that is believed to underlie these biases is long-lasting, which makes an individual vulnerable to relapse long after initial cessation. In smokers, increased reactivity to smoking cues has been found to predict decreased likelihood of cessation [13, 14]. Consequently, reduction in cognitive bias is considered a promising target for therapeutic intervention.

Recent research indicates that it is possible to reduce cognitive biases using computer-based cognitive bias modification (CBM) paradigms that train individuals to allocate attention away from disorder-relevant cues. CBM has been shown to reduce cognitive biases in anxiety and depression [15–17] and has also been associated with reduction in other symptoms [18]. Attwood *et al*. [19] investigated the effect of a single session of stimulus-avoidant CBM using a modified dot-probe task, and reported decreases in cognitive bias in daily smokers. Compared to a group who had been trained to attend to smoking cues, there was evidence that the avoid group also showed attenuated craving in response to *in vivo* smoking cues in a subsequent cue exposure test (male participants only). The current study will extend earlier work by investigating the neural responses to smoking-related cues following CBM. The neuroimaging literature suggests that drug-related cognitive biases are the results of a failure of cognitive regulatory systems to increase control in the presence of salient cues that increase processing in the reward and emotional centers of the brain (such as the striatum and amygdala) [20]. These data will enable the investigation of whether CBM decreases emotional responses to drug-related cues or increases cognitive control in their presence, and will thereby increase understanding of the mechanisms that underlie CBM effects.

There has been a recent suggestion that the smoking cessation pharmacotherapy varenicline reduces cue-induced craving and cue-induced reinstatement of drug-taking in animals [21–24]. This study will include a pharmacological challenge that randomizes participants to receive seven days treatment of either varenicline or placebo prior to a functional Magnetics Resonance Imaging (fMRI) scan, in order to assess neural cue-reactivity following varenicline treatment. Previous research has reported differences in neural response to smoking cues following varenicline treatment [25], but the sample sizes were small and the effects require replication.

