### Participants and recruitment

Current smokers (n =72; 50% male) will be recruited from the staff and students at the University of Bristol (United Kingdom) and the general population. A CONSORT diagram of participant recruitment is shown in Figure 1. Participants will be recruited through existing email lists and poster and flyer advertisements, and by word of mouth. Participants who are interested in taking part will be sent the study information sheets and a telephone screening will be arranged to assess basic eligibility. Those who meet the study inclusion criteria will be booked in for two sessions approximately one week apart. Participants will receive £70 compensation for their time for participation. Full written informed consent will be obtained from each participant at the start of the study session. Participants will be given a copy of the information and consent form to keep.

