### Sample size determination

As our primary objective is to investigate the effects of CBM training on neural response to smoking-related cues, the sample size determination was based on this outcome. However, the effects of cognitive bias on neural responses to smoking cues have not been evaluated in previous research. To estimate the required sample size we used data from our previous study [19] that indicated a likely increase in the cognitive bias index of 30 ms in the attend group, and a decrease of 30 ms in the avoid group. We assume that the change in the control condition will be intermediate (0 ms). We will therefore achieve greater than 80% power to detect a linear effect across the three CBM groups on change in cognitive bias index with a total sample size of n = 30, at an alpha level of 0.05. Using data from a study that compared craving in response to smoking cues in groups who had received treatment of varenicline (mean = 11.2, standard deviation = 4.7) versus placebo (mean = 14.6, standard deviation = 4.7), we estimate a total sample size of 64 is required to achieve 80% power at an alpha level of 0.05. As we expect some attrition, we will use a more conservative estimate of n = 72.

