### Randomization

Participants will be randomly assigned to drug and CBM groups, but equal numbers of participants per group will be maintained. The drugs will be prepared by University Hospitals Bristol Pharmacy who will produce two batches of 36 bottles (one for males and one for females) that comprise 18 bottles of varenicline and 18 bottles of placebo. Each bottle will be given a numeric identifier that enables study staff involved in data collection to be fully blinded to drug condition.

In advance of the study, an experimental collaborator (who will have no direct contact with the study participants) will prepare a numeric code using random number assignment software to further randomize participants to CBM groups. Randomization will be stratified so that equal numbers of male and female participants will be allocated to each experimental cell.

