Each participant’s fMRI data will then be entered into a first-level voxel-by-voxel analysis using the general linear model. Each cue block (smoke or control) will be modelled as a boxcar function convolved with a canonical hemodynamic response function that begins at the onset of the first cue in the block and ends at the end of the block (60-second duration). A high-pass filter will be applied to remove slow signal drift. A smoking-related cue greater than control cue contrast image will then be created and inputted into a random effects analysis. A two (varenicline and placebo) × three (attend, avoid, and control) mixed-model analysis of variance (ANOVA)will be used to examine smoking cue reactivity (smoking greater than control) between each group. Voxel-wise analysis will be conducted within an Region of Interest (ROI) mask. The mask will be created from anatomical regions identified in a meta-analysis of cue reactivity [31]: nucleus accumbens, caudate, putamen, temporal gyrus, anterior cingulate gyrus, amygdala, insula, posterior cingulate cortex, inferior frontal gyrus, and angular gyrus. Each bilateral region will be selected using the WFU PickAtlas tool [32] and combined to create the mask. Resulting activations will be considered significant at an alpha level of 0.001 (uncorrected) with a minimum cluster extent threshold of 20 contiguous voxels. *Post hoc* analyses of parameter estimates will be used to evaluate the nature of significant effects. Smoking cue greater than control cue contrast images for each participant will also be input into random effect regression analyses examining relations between post-training cognitive bias scores and neural cue reactivity.

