#### Cognitive bias analyses

Cognitive bias scores will be calculated from reaction time (RT) data from the visual probe task, by subtracting RTs to probes that replace smoking-related pictures from RTs to probes that replace neutral pictures, so that positive scores represent a bias towards smoking cues and negative scores represent a bias towards neutral cues. These bias scores will be used to examine cognitive training effects in a two (pre- and post-CBM) × two (varenicline and placebo) × three (attend, avoid, and control) mixed-model ANOVA.

A two (smoking cue and neutral cue) × two (pre- and post-CBM) × two (varenicline and placebo) × three (attend, avoid, and control) mixed-model ANOVA will also be conducted on the modified Stroop task RT and error data. Participants will be excluded if their mean RT or error score is three standard deviations (or more) below or above the sample mean.

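### Sex is a stratification factor, and the earlier study saw the CBM effect on cue-induced craving in men only, but the listed models give sex no place; a men-only effect on cue response would be diluted

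*Protocol article*

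**What the plan says.** The Background reports two results from the earlier study. For bias, it "reported decreases in cognitive bias in daily smokers", with no restriction by sex. For craving, the avoid group responded less than the attend group to "smoking cues in a subsequent cue exposure test (male participants only". The Background says the present trial builds on that work by measuring neural responses after CBM. *Sample size determination* relies on the same study for planning ("we used data from our previous study [19").

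Sex is controlled by design. *Participants and recruitment* has "Current smokers (n =72; 50% male) will be recruited", and *Randomization* has "Randomization will be stratified so that equal numbers of male and female participants will be allocated to each experimental cell". The pharmacy also prepares a separate batch of bottles for each sex.

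The *Statistical plan* names the factors of each model:
- For the neural outcome, a drug by CBM "mixed-model analysis of variance (ANOVA)will be used to examine smoking cue reactivity (smoking greater than control) between each group".
- For dot-probe bias, a "two (pre- and post-CBM) × two (varenicline and placebo) × three (attend, avoid, and control) mixed-model ANOVA".
- For craving and mood across CBM, the same three factors (*Questionnaire analyses*).

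Sex is not a factor, covariate or modifier in any of these, and no hypothesis mentions it. The one modifier the article says it will explore is varenicline.

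**The concern.** The primary objective is the effect of CBM on neural response to smoking cues. The only evidence in smokers that the article describes for CBM changing a response to cues comes from its own earlier study, and there the effect was reported in men only. The listed models estimate one common CBM effect across the sexes. If the effect differed by sex, that estimate would be an average of two different effects. A null result could then hide an effect in men, and a positive result could be claimed for daily smokers in general.

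A sex main effect alone would not show this, because it still assumes the same CBM effect in both sexes. The stratified allocation already supplies the data for a sex-specific estimate, but the listed analyses do not use it.

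**Working it through.** **The plan's own figures.** The varenicline calculation (means 11.2 and 14.6, SD 4.7) gives a standardised difference of 3.4/4.7 = 0.72. A two-sided t-test at 0.05 with 80% power needs 31 per arm, or 62 in total, close to the stated 64. The CBM figure of n = 30 cannot be reproduced because no SD is given. It concerns dot-probe bias and is not split by sex. Neither figure supplies an effect size for CBM on neural response, so that effect, d, is assumed below.

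**Inputs.** There are 72 participants, half of them men, and 24 per CBM arm (*Cognitive bias modification*). With sex balanced in each cell, that is 12 men and 12 women per CBM arm. Let the attend-minus-avoid effect be d in men and r × d in women, in within-cell SD units. Error df are 72 − 12 sex by drug by CBM cells = 60.

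**Standard errors.**
- Pooled attend minus avoid: √(2/24) = 0.289
- Within one sex: √(2/12) = 0.408
- Men minus women: √(4/12) = 0.577

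**Pooled estimate.** d(1 + r)/2, with non-centrality d(1 + r)/(2 × 0.289). Power is from the non-central t.

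| Effect in women (d = 1.0 in men) | Pooled estimate | Non-centrality | Power, two-sided 0.05 |
|---|---|---|---|
| None (r = 0) | 0.50 | 1.73 | 40% |
| Half (r = 0.5) | 0.75 | 2.60 | 72% |
| Equal (r = 1) | 1.00 | 3.46 | 93% |

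Across d = 0.75 to 1.5, men-only pooled power runs from 25% to 72%. Keeping the listed drug by CBM model (66 df, with the sex difference left in the error) gives 39% in place of 40% at d = 1.0, so the choice of error term hardly matters. With 21 per arm after attrition it is 36%.

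**Sex-specific contrasts at d = 1.0, two-sided 0.05.**
- Within men: non-centrality 1.0/0.408 = 2.45, power 67%.
- CBM by sex, no effect in women: 1.0/0.577 = 1.73, power 40%.
- CBM by sex, half effect in women: 0.5/0.577 = 0.87, power 14%.

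**At the neural threshold.** The plan tests voxels at 0.001 uncorrected, with a 20-voxel extent. Taking one voxel, one-sided, d = 1.0 and no effect in women, power is about 8% pooled, 23% within men and 8% for CBM by sex. The extent rule and the number of voxels are not modelled, so these figures are indicative only.

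**Precision of the sex-specific estimates.** The 95% half-widths are 2.00 × 0.408 = 0.82 SD within one sex and 2.00 × 0.577 = 1.15 SD for the difference between the sexes.

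**The case against.** **The article is condensed.** A supportive moderator analysis is something an article may leave to a fuller plan that is not shown, and no passage contradicts another. The pooled contrast properly estimates the average effect in a sex-balanced sample, which fits an objective stated for daily smokers. This stands in part: the pooled test is not wrong, and a supportive analysis may exist elsewhere. But the article names the factors of each model, and the stratification factor is visibly absent from them.

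**The outcome differs.** The men-only result was self-reported craving to in vivo cues. Neural response to pictures is another measure, and craving is secondary here. This stands: applying the pattern to the neural outcome is an inference.

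**Halving is the extreme case.** The Background gives neither the estimate in women nor any test of the difference between the sexes. An effect reported in men does not establish that women had none. With half the effect in women, the pooled test (72%) has more power than the test within men (67%).

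**The remedy is weak at the voxel threshold.** Repeating the planned mask and threshold for CBM by sex would be nearly uninformative at about 8%, and a voxel-wise map does not yield a single estimate with an interval. This stands and shapes the fix.

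**Stronger readings to avoid.** A reader might infer that every planned CBM analysis is compromised, the dot-probe included. The documents do not support that, because the bias decrease carries no sex restriction and the ±30 ms planning values are not split by sex. A reader might also infer that the CBM effect will be halved, or that the trial can settle whether it differs by sex. The first needs a zero effect in women, which the documents do not state. The second is contradicted by the power figures.

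**Conclusion.** The concern holds in a limited form, for neural cue reactivity and craving only. The article reports a sex-specific CBM signal on a related outcome and stratifies by sex, but then lists models in which sex plays no part. If the pattern carried over, pooled power at d = 1.0 would fall from about 93% to somewhere between 72% (half the effect in women) and 40% (no effect). In the men-only case it would be about 8% at a single voxel tested at 0.001.

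These figures rest on an assumed d, an assumed effect in women, the full 24 per CBM arm, and the inference from craving to neural response. They show a risk of misreading the pooled result. They do not predict that it will be null.

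**What to change.** - Keep the pooled CBM effect as the main test.
- Include sex in the models, since it is a stratification factor.
- Pre-specify one supportive CBM by sex analysis for neural cue reactivity and for craving. Report attend minus avoid in men, in women, and the difference between them, with confidence intervals, whatever the pooled result.
- For the neural outcome, base this analysis on mean parameter estimates extracted from the anatomical regions already defined for the mask, and name in advance which regions or combination will be used. This gives one estimate and interval per contrast, which a thresholded map does not.
- Leave the dot-probe analysis out of the supportive CBM by sex analysis.

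The cost is wording in the analysis plan. Sex is already used for allocation, and no further data or participants are needed. The downside is one extra low-powered contrast per outcome, with 12 per sex per CBM arm. It must be labelled supportive and not serve as a second route to a positive result. A non-significant CBM by sex contrast must not be read as showing that the sexes respond alike.

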### Study objectives and hypotheses

The primary objective is to investigate the neural effects of CBM in response to smoking-related cues in current daily smokers. A secondary objective is to examine the effects of varenicline treatment on neural responses to smoking cues. We will also explore whether there is any pattern in the data to suggest that the effects of CBM are modified by concurrent treatment with varenicline. The CBM methods we will use are delivered via computer, and can therefore in principle be delivered remotely and repeatedly at low cost, for example via the internet or smartphones, as an adjunctive treatment to varenicline pharmacotherapy. To investigate whether CBM and varenicline effects generalize to other measures of cognitive bias, participants will also complete a modified pictorial Stroop task before and after CBM and varenicline.

We hypothesize that: 1) CBM designed to induce cognitive bias towards smoking-relates cues will lead to an increase in cognitive bias and neural response to smoking-related cues in brain regions previously implicated in cue reactivity in cigarette smokers; 2) CBM designed to induce cognitive bias away from smoking-relates cues will lead to a decrease in cognitive bias and neural response to smoking-related cues in brain regions previously implicated in cue reactivity in cigarette smokers; and 3) varenicline treatment will lead to a reduction in the neural response to smoking-related cues.

## Methods/Design

### Trial design

This is a human laboratory study assessing behavioral and neural outcomes of CBM. The study design is a two × three between-subjects model with one factor of drug (varenicline or placebo) and one factor of CBM group (attend, avoid, or control). For the behavioral assessments of cognitive bias (dot-probe and modified Stroop) and cue reactivity (cue exposure task in scanner), there will be an additional within-subjects factor of cue type (smoking or neutral).

### Participants and recruitment

Current smokers (n =72; 50% male) will be recruited from the staff and students at the University of Bristol (United Kingdom) and the general population. A CONSORT diagram of participant recruitment is shown in Figure 1. Participants will be recruited through existing email lists and poster and flyer advertisements, and by word of mouth. Participants who are interested in taking part will be sent the study information sheets and a telephone screening will be arranged to assess basic eligibility. Those who meet the study inclusion criteria will be booked in for two sessions approximately one week apart. Participants will receive £70 compensation for their time for participation. Full written informed consent will be obtained from each participant at the start of the study session. Participants will be given a copy of the information and consent form to keep.

**Figure 1 Fig1:**
[figure not shown]
**CONSORT flow diagram.** CBM, cognitive bias modification.

### Study setting

All study sessions will be run at the Clinical Research and Imaging Centre at the University of Bristol, United Kingdom.

### Inclusion criteria

For inclusion, participants should be aged between 18 and 40 years, smoke at least 10 manufactured or 15 roll-up cigarettes per day, and smoke within one hour of waking in the morning. They should report availability to attend all of the study sessions and be able to adhere to all study requirements (including adhering to the seven-day drug administration regimen). Participants should have English as a first language, or have an equivalent level of fluency, and be able to give informed consent.

### Exclusion criteria

Participants will be excluded from this study if they have current or past alcohol or drug misuse and/or dependence, psychiatric illness, or clinically significant abnormality (including cardiovascular risk factors). Participants should not have ongoing use of any medication (at least eight weeks clear of any prescribed medication). Female participants should not be pregnant, breastfeeding, or at risk of becoming pregnant (not using adequate contraception). All participants must be registered with a GP, should not consume more than eight caffeinated beverages per day or more than 35 alcoholic units per week if female, or 50 alcoholic units per week if male (1 unit = a half pint (284 ml) of ordinary strength (3.5 to 4% alcohol-by-volume (ABV)) beer, a small glass (125 ml) of 8% ABV of wine, or a single measure (25 ml) of a 40% ABV spirit). They should not be actively trying to give up smoking and not be planning to quit during the study period. They should not have an uncorrected visual (including colour blindness) or auditory impairment or any known hypersensitivity to varenicline. Finally, they should not have any condition that would make magnetic resonance imaging (MRI) scanning unsafe or intolerable (such as metallic implants).

